## Abstract

**Background:**

A core feature of chronic obstructive pulmonary disorder (COPD) and chronic heart failure (CHF) is that symptoms may change rapidly because of illness progression. Thus, these chronic conditions are associated with high rehospitalisation rates. Person-centred care (PCC) has been shown to have several benefits for patients with COPD or CHF (or both disorders) but it has not yet been investigated through e-health services.

**Aim:**

The project aims to evaluate the effects of PCC by a combined digital platform and structured telephone support for people with COPD and/or CHF.

**Methods and analysis:**

A randomised controlled trial with open, parallel groups which employs a participatory design process will be used. This project will also include process and health economic evaluation of the intervention.

**Ethics and dissemination:**

Ethical approval has been secured from the Regional Ethical Review Board in Gothenburg, Sweden (Dnr 063-17 and T063-18). Results will be presented at conferences and to healthcare professionals, participants and patient organisations. Findings will also be submitted for publication in peer-reviewed journals.

**Trial registration number:**

NCT03183817

Strengths and limitations of this studyThis project is the first randomised controlled trial to evaluate the effects of person-centred care by a combined digital platform and structured telephone support for people with chronic obstructive pulmonary disorder and/or chronic heart failure.The protocol details a complex intervention aimed at operationalising person-centred ethics.To answer the research questions of the study, collected data will be analysed using quantitative and qualitative methods.The evaluation will include patient-reported outcome measures together with health economics and process outcomes.Unfortunately, this study did not include individuals without a device for the internet and those who could not read or write in Swedish.

## Introduction

Chronic heart failure (CHF) and chronic obstructive pulmonary disease (COPD), two long-term conditions common in older populations, are associated with high rehospitalisation rates and high mortality.^1 2^ In addition, both conditions severely affect activities of daily living because of frequent symptoms that limit health-related quality of life (HRQoL), compelling patients to be dependent on others.^3^ Patients with CHF and/or COPD frequently require hospital care and the severity of their symptoms often leads to repeated visits to hospital, outpatient or primary care.^1–3^ Although pharmacological therapy has improved outcomes markedly over the past 10–15 years, management programmes are still needed to optimise care.^4^ There are benefits of pulmonary rehabilitation (eg, reduction in readmission and mortality), including exercise training, education and self-management interventions that specifically target behaviour change for patients with COPD.^5^ A consistent recommendation in the treatment of CHF is management programmes designed to improve outcomes through structured follow-ups that increase patients’ self-care skills and other key issues (eg, symptoms and disease trajectory).^2^ Being affected by a chronic disease with a high symptom burden is a major challenge to living a full life. Healthcare professionals (HCPs), such as registered nurses, occupational therapist and physiotherapist, in conjunction with well-developed technology, can serve to enable successful self-management for individuals with severe long-term illnesses.^6^

### Person-centred care

The basis of person-centred care (PCC) is to include the patient’s experience, situation, capabilities and resources in the care process. PCC highlights the importance of understanding the person behind the patient as a human being with reason, will, emotions and needs in order for that person to be able to be an active partner in his or her care and treatment.^7^ Patients (often with the help of relatives) present themselves as persons by expressing their illness narrative. This narrative includes how daily life events are being affected by the condition and treatment and creates a starting point for collaborative care and partnership between HCPs and patients which encourages and empowers patients to actively take part in finding solutions to their problems.^7 8^ PCC entails not only to identify health barriers but also to confirm human capabilities and opportunities in the patients’ home and local environment. PCC is based on ethical principles, inspired by the capability approach (an alternative approach to welfare economics), which has also been used in research as a theoretical frame of reference in several disciplines (eg, in economics by the Nobel Laureate Amartya Sen).^9^ All people develop their capabilities (such as a sense of responsibility for oneself and others) in relation to other people.

Previous studies evaluating PCC that, for example, uses personal health plans and symptom tracking have shown positive effects in patients with several conditions, both acute and long term, and in different care settings. Positive outcomes include shortened hospital stays,^10^ reduced readmittance,^11^ improved self-efficacy,^12^ reduced healthcare costs,^13 14^ maintained functional performance,^10^ improved HRQoL,^11^ improved pain management, greater stamina and enhanced self-reported health,^15^ increased physical activity,^16^ improved self-efficacy to manage symptoms,^17^ reduced fatigue and anxiety^15^ and improved experience of the care.^18^ Moreover, effects have been especially prominent in patients without postsecondary education,^19^ an effect that was sustained for up to 2 years.^20^ These studies have applied a PCC approach in practice, wherein the needs of the patients are important which also incorporate their human ability, which is an often underused resource in healthcare.^7 21 22^

### E-health

To meet demands on accessible and efficient care, one suggestion is to facilitate the partnership between HCPs and patients.^23^ One such effort can be the care and support provided through e-health. At present, the internet is frequently used as a source of information and Sweden belongs to the countries that is high up in the development of maturity of internet use concerning the number of computers and the possibility of accessing the internet.^24^ Digital web-based care has no geographical constraints, that is, it is potentially accessible everywhere. It also affords the possibility to reach persons who at present avoids to seek help because they find it stigmatising.^25^ Moreover, the possibility of having contact with HCPs in privacy, when one has the time and when questions arise, is found to be important.^26^ Many people want to manage their health by themselves, especially when they are concerned about their illness. Yet people yearn to be understood and they communicate with others with similar experiences.^26^ E-health solutions offer these possibilities. Digital health interventions have also been shown to hold promise to improve the quality and experience of care for patients with CHF.^27^

There are, however, some concerns that need to be taken into account when designing e-health solutions. There are some indications that older people can find e-health solutions difficult to handle.^28^ Previous research have also shown that e-health support, in which the users are not directly involved in the process, has low impact.^29^

There is some research combining e-health with PCC. PCC in the form of a structured telephone support for patients with CHF and/or COPD has been shown to mitigate worsening self-efficacy without increasing the risk of clinical events.^30^ Using a digital symptom tracking tool in combination with PCC has been found to improve general self-efficacy compared with standard care.^31^ E-health interventions that are developed using a participatory design and that use personal resources are also consistent with the ethics expectations of PCC. Overall, e-health solutions are considered a promising approach to strengthen self-management among patients with CHF or COPD.^29^ There is, however, a need for studies investigating the effects of PCC via e-health solutions for people with long-term illness.

## Aim

The project aims to evaluate the effects of PCC by a combined digital platform and structured telephone support for people with COPD and/or CHF.

## Methods/design

The design will be a randomised controlled trial (RCT) with open parallel groups. In addition, the project will include process and health economic evaluations of the study. Thus, the project will integrate the collection and analysis of both qualitative and quantitative data to answer the research questions. User experiences and process evaluations are necessary complements to each other to help understand more about enablers and barriers to self-management support using a combined digital platform and telephone support. The protocol complies with the Standard Protocol Items: Recommendations for Interventional Trials.^32 33^

### Patient and public involvement

Public involvement is a cornerstone in PCC. Therefore, this study incorporates a participatory design that assumes that all users (patients, relatives and HCPs) are involved in the study design, which has been reported to facilitate implementation.^34^ Extensive consultation with members of the community took place during the development of the digital platform and design of the study. During these consultations, the patient representatives requested that the platform should include functionalities such as ability for two-way communication, reliable information and advice about their condition and that it should be user friendly. The HCPs contributed with input concerning layout and technical functionalities of the platform. An advisory group consisting of patient representatives, relatives, HCPs, system developers and researchers was formed to provide advice and codesign all of the major elements of the study design.

### Participants and setting

Study participants who fulfil the inclusion criteria of the study will be recruited from nine public primary care centres in Gothenburg.

#### Inclusion criteria

Diagnosed with COPD or CHF.Listed at one of the nine participating primary care centres.Must understand written and spoken Swedish.

#### Exclusion criteria

No device with internet access, that is, no computer, smartphone or tablet.Severe impairment that prevents persons from using e-health support.No registered address.Any severe disease with an expected survival of <12 months.Cognitive impairment.Ongoing documented diagnosis of alcohol/drug abuse.Other diseases that can interfere with follow-up (eg, severe depression and other severe mental illnesses).Participating in another conflicting study.

#### Enrolment and randomisation

Designated HCPs will screen medical records of listed patients at the participating primary care centres against study inclusion and exclusion criteria. Eligible patients will be sent a letter informing them about the study. The HCPs then contact the eligible patients through phone to give further information about the study and ask whether they are willing to participate. If the patient agrees to participate, a consent form together with a return prepaid envelope will be sent to the patient. Once the consent form is returned to the HCPs, patients will be randomised to usual care or PCC plus usual care. The randomisation will be based on a computer-generated list created by a third party. All patients will be informed about group assignments through phone.

#### Usual care

Patients randomised to usual care will be managed by regular evidence-based treatment and care as outlined in treatment guidelines.^2 5^

#### Design of intervention

The intervention is based on the theoretical PCC framework in which all people are seen as capable with a unique understanding of themselves and who have unique experiences, expectations, needs, preferences and resources. A central component of PCC is that the professional and patient jointly develop a personal health plan using resources identified in each patient’s illness history as well as defining potential barriers to effective care.^7^ Self-efficacy as a concept is closely related to PCC as it also refers to people’s belief in their capability to affect daily life events.^7 31 35^ In addition, self-efficacy has been shown to have important implications for patient recovery,^36^ which is related to the fact that patients confident in their ability to manage everyday life are likely to engage in rehabilitation more actively.^7 35^ Steps and components of the intervention are described as follows.

#### Description of intervention elements

When the HCPs call the participants in the intervention group to inform them about the outcome of the randomisation procedure, the HCPs will also describe the intervention, assist the participants in creating a login to the platform and describe its features and decide on a date and time for a phone call when the healthcare plan is created. All the dedicated HCPs participated in the development of the digital platform and received special training in performing PCC communication at a distance. Access to the digital platform will be password protected.

#### Telephone support and health plan

When the HCPs call the participants, they listen to their narrative about daily life events and how they are affected by the condition, what kind of problems they experience and what resources they have to cocreate the health plan. The HCPs try to encourage narration and establish a partnership by using PCC communication skills such as open-ended questions, reflections and summaries. Based on the patient narrative, patient goals, resources and needs are identified and communicated with the patient (participant). The participant (sometimes together with relatives) and the HCPs formulate a person-centred health plan in partnership. The health plan contains five elements:

Today we have talked about.You would like to be able to do/feel.To get there you have to.Capabilities and resources that could help you are.Support that you might need is.

The health plan will be based on mutual agreement between the patient and HCPs and contains the patient’s goals, resources and support needs. It also contains follow-up actions and steps needed to achieve progress in the care of the patient. The date of follow-up conversations will be scheduled jointly. This plan will be uploaded to the digital platform with help from the HCPs if the participants have chosen to write the plan themselves or it will be written directly by the HCPs and then finalised when accepted by the participants.

The health plan will be the point of departure for the forthcoming conversations and communication via the platform that the participants and the HCPs will have during the study period (of 6 months). The plan will be considered during each follow-up when the HCPs contact the participants and revised when necessary. During the intervention, the participants will also be free to contact the HCPs during office hours.

#### Digital platform

The platform will contain headings, such as messages, daily ratings, health plan, contact, next of kin and links, when logged in that may inspire the patients to make notes on ‘a good day’ and ‘a bad day’, respectively. Functionalities of the platform include ability for two-way communication, possibility to rate symptoms and a collection of links to information concerning COPD and CHF. Symptom ratings and comments will also be made to create a graph over time once the daily ratings have been completed. The HCPs will be able to see the patients’ accounts and make comments. The patients will be able to add or delete any person (eg, informal carers, family or friends) to whom they would like to give access to their account. The patients will also be able to customise what content they want visible for invited persons. For instance, they could choose to restrict visibility of the messages between themselves and the HCPs or elect to show all contents in their account such as the health plan and daily ratings.

The digital platform will also contain a function to send private messages between the participants and the HCPs. The HCPs check for new messages daily. Another function offered in the platform will be the possibility to link relevant information about CHF and COPD which is provided by patient organisations (eg, the heart and lung association) and the Swedish national help guide (1177.se). There will also be links to a peer-to-peer support group.

#### Sources and collection of data

Data will be collected using self-report instruments, interviews, study documentation, medical records and administrative registers. Questionnaires will be mailed (together with a prepaid return envelope) to the participants at study inclusion and 3, 6, 12 and 24 months after randomisation. Paper questionnaires were chosen since not all of the instruments are validated for online use. Follow-ups and adverse events (ie, admission to hospital or death) will be controlled for all participants. Baseline data (including demographics, characteristics and medical history) will be collected from the patients’ medical records. For details, see figure 1.

**Figure 1 F1:**
[figure not shown]
Timeline of the intervention and data collection. HCPs, healthcare professionals.

#### Questionnaires

The General Self-Efficacy Scale.^37^EuroQol-5 Dimensions health state questionnaire (EQ-5D).^38^Hospital Anxiety and Depression Scale (HADS).^39^Shortness of Breath in Heart Failure (SOB-HF).^40^COPD Assessment Test (CAT).^41^The Medical Research Council (MRC) breathlessness scale.^42^

#### Primary end point

The primary end point will be the composite score of change in general self-efficacy and rehospitalisation or death 6 months after randomisation.

A patient will be classified as deteriorated if:

General self-efficacy has decreased by ≥5 units.Patient has been hospitalised for unscheduled reasons due to COPD/CHF.Patient has died due to all causes.

A patient is classified as improved if:

General self-efficacy has increased by ≥5 units.Patient has not been hospitalised due to COPD/CHF.Patient has not died.

Those who have neither deteriorated nor improved are considered unchanged.

#### Secondary end points

Number of admissions.General self-efficacy.^37^Healthcare utilisation measured as the number of admissions and unscheduled outpatient visits due to unplanned visits to hospital or primary care centre due to symptoms of COPD or CHF.HADS.^39^HRQoL (EQ-5D).^43^Incremental cost-utility ratios.Comparing HRQoL and costs for healthcare.CAT.^41^The MRC breathlessness scale.^42^SOB-HF.^40^

#### Project timeline

Recruitment of participants commenced in August 2017 and was completed in June 2019. During this period, 224 eligible patients had been identified and included in the study. The intervention will continue until early 2020 after which data for the primary outcome will be collected. Data collection for the secondary outcome measures will continue until mid-2021.

#### Power calculation

To achieve 80% power based on a p value of 0.05 (two-tailed) for an increase in the proportion of improved patients from 20% to 40% in the primary outcome, a sample size of 91 patients in each group is required. However, we plan to include 110 patients in each group to have some margin for withdrawals/dropouts. Thus, a minimum of 220 patients will be randomised across the two groups.

#### Quantitative data analysis

Descriptive statistics will be used to characterise the study groups. Between-group differences will be tested using Fisher’s exact test for dichotomous variables and parametric and non-parametric tests will be used for continuous variables. Logistic regression will be used to calculate odds ratios with 95% CIs. Statistical significance will be set to p<0.05 (two-sided). Both intention-to-treat and per-protocol analyses will be conducted. In addition, subgroup analyses will be performed.

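### The proportion improved is, on the natural reading, tested with Fisher's exact test but estimated by logistic regression; one logistic model adjusted for baseline self-efficacy would align p-value and interval and gain power

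*Protocol article*

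**What the plan says.** All places are in the protocol article.

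- **Quantitative data analysis.** Between-group differences are tested with Fisher's "exact test for dichotomous variables and parametric and non-parametric tests will be used for continuous variables". A separate sentence adds: "Logistic regression will be used to calculate odds ratios with 95% CIs". No covariates are listed, and the test for the primary end point is not named.
- **Power calculation.** The trial is sized for "an increase in the proportion of improved patients from 20% to 40% in the primary outcome", and "a sample size of 91 patients in each group is required" at 80% power and two-sided 5%. The plan is 110 per group to allow for losses.
- **Primary end point.** Patients are classed as deteriorated, unchanged or improved at 6 months. To be improved, a patient must gain at least 5 units of general self-efficacy, with no hospitalisation for COPD or CHF and no death.
- **Sources and collection of data.** Questionnaires are mailed "at study inclusion and 3, 6, 12 and 24 months after randomisation", so every scale has a baseline value.

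**The concern.** Two things follow if Fisher supplies the primary p-value and logistic regression the odds ratio and interval.

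First, they are different methods, and the text does not say which governs. In a borderline result the reader could be shown an interval that excludes 1 beside a p-value above 0.05.

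Second, Fisher's test has no place for a covariate. The improved class is defined by change from baseline, but that does not use up the information in the baseline score. A patient who starts low is more likely to rise by 5 units, through regression to the mean and room on the scale, and one who starts near the top may be unable to. Baseline therefore remains prognostic for the class, and leaving it out gives up power for which the data are already being collected. The same holds for the continuous scales if they are compared without their baseline values.

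**Working it through.** **Inputs from the article:** 20% versus 40% improved, two-sided 0.05, 80% power, 91 required and 110 planned per group. **Assumed, because the article does not give them:** the correlation r between baseline and follow-up scores, the standard deviation and mean of the self-efficacy score, and the share of patients kept out of the improved class by events.

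**1. Reproduce the plan's figure.** With p1 = 0.2, p2 = 0.4, mean 0.3 and d = 0.2:

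n = [1.96·√(2·0.3·0.7) + 0.8416·√(0.2·0.8 + 0.4·0.6)]² / 0.2² = (1.2702 + 0.5323)² / 0.04 = 81.2, so 82.

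With continuity correction: n' = (n/4)·[1 + √(1 + 4/(n·d))]² = 20.31 × (1 + √1.246)² = 90.95, so **91**. This matches the plan. Exact Fisher power at 91 per arm is 80.8%, so the stated size fits an unadjusted Fisher test.

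**2. Fisher against the logistic interval.** Every possible 2×2 table was enumerated, comparing Fisher p<0.05 with the Wald 95% interval from logistic regression without covariates.

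| True proportions | n per arm | Fisher significant | Interval excludes 1 | Disagree |
|---|---|---|---|---|
| 20% v 40% | 91 | 0.8076 | 0.8418 | 0.0342 |
| 20% v 33% | 91 | 0.4525 | 0.5085 | 0.0560 |
| 20% v 20% | 91 | 0.0327 | 0.0489 | 0.0162 |
| 20% v 40% | 110 | 0.8794 | 0.9056 | 0.0262 |
| 20% v 33% | 110 | 0.5339 | 0.5906 | 0.0567 |
| 20% v 20% | 110 | 0.0339 | 0.0477 | 0.0138 |

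In every scenario run, all the disagreement is in one direction: the interval excludes 1 and Fisher is not significant.

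**3. One such result.** With 18 of 91 versus 30 of 91 improved:

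- OR = (30×73)/(61×18) = 2190/1098 = 1.99.
- SE of log OR = √(1/18 + 1/73 + 1/30 + 1/61) = 0.345.
- 95% CI = exp(0.690 ± 1.96×0.345) = 1.01 to 3.92.
- Fisher p = 0.064.

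At 110 per arm, 22 versus 35 gives OR 1.87, CI 1.01 to 3.46, and again Fisher p = 0.064.

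**4. Gain from baseline on the primary end point (simulation under assumptions).** Self-efficacy was simulated on a 10 to 40 scale with mean 28, SD 5 or 6 and r from 0.4 to 0.8. Events removed 0% or 15% of patients from the improved class. Each setting was calibrated to 20% versus 40% improved at 91 per arm and run for 1,500 trials. A power near 0.8 then has a Monte Carlo standard error of √(0.8×0.2/1500), about 1 point. Across settings:

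- baseline-adjusted minus unadjusted logistic regression: about 2 to 7 points of power;
- baseline-adjusted logistic regression minus Fisher: about 6 to 11 points.

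The difference between these two ranges is what is gained merely by leaving a conservative exact test. Only the first is due to using baseline. The gain is largest at low r.

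**5. Continuous scales.** The variance with the baseline score as covariate is 1−r² of a follow-up-only comparison and (1+r)/2 of a change-score comparison.

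| Assumed r | Versus follow-up only | Versus change score |
|---|---|---|
| 0.3 | 0.91 | 0.65 |
| 0.5 | 0.75 | 0.75 |
| 0.7 | 0.51 | 0.85 |

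**The case against.** The strongest reply is that this is one short paragraph of a journal article and that much of the concern is inference. Several parts of that reply stand.

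- **Unadjusted throughout?** A reader might infer that no analysis uses baseline. The article does not say so. The parametric tests are unnamed and could include ANCOVA, and the logistic model could carry covariates. Only Fisher is unadjusted by its nature.
- **Fisher as the primary test?** This too is inferred. The end point has three classes, and only the power calculation reduces it to the proportion improved. The reading is natural, and the match of 91 to a Fisher-type calculation supports it.
- **Separate tests at each visit?** A reader might infer these from the five measurement times. The article does not say how visits are handled, and a repeated-measures specification is ordinary analysis-plan content.
- **Chance imbalance from simple randomisation?** Enrolment and randomisation mentions a computer-generated list from a third party and is silent on blocking and stratification. Silence does not show that there is none. Even simple randomisation gives a valid test.
- **Size.** The disagreement touches only borderline results. Fisher errs on the cautious side, so false positives are not inflated if it governs. The article also reports that "224 eligible patients had been identified and included in the study"; with few losses Fisher already has 87.9% power at 110 per arm.

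The reply does not remove the point. On dichotomous variables the section is not silent: it names one method for the test and another for the interval. If the logistic model does carry covariates, the mismatch grows, because its conditional odds ratio is not what Fisher tests.

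**Conclusion.** The point holds as one of efficiency and consistency, not validity. As written, the proportion improved is naturally tested by a conservative test that cannot use baseline, beside an interval from another method.

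Against a logistic model without covariates, the two give opposite verdicts in 3.4% of trials at the design effect and 5.6% at 20% versus 33% (91 per arm). These figures need no outside input.

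The power gain from baseline, about 2 to 7 points over unadjusted logistic regression and 6 to 11 over Fisher, rests on the assumed correlations, standard deviations and event shares. Its direction is the same in every setting tried, but its size cannot be fixed from the article. It would be wrong to credit the whole distance from Fisher to the adjusted model to baseline, since part of it is Fisher's conservatism. For the continuous scales, any loss depends on whether the unnamed tests already use the baseline score.

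**What to change.** In Quantitative data analysis, name one primary analysis: a logistic regression of improved versus not improved at 6 months, with arm, baseline General Self-Efficacy score and diagnosis (COPD, CHF or both) as covariates, giving both the p-value and the 95% CI. Keep Fisher's exact test as a sensitivity check. State that the continuous scales are compared with their baseline score as covariate, by ANCOVA or an equivalent model.

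The cost is wording, settled before the primary-outcome data are analysed. The baseline questionnaire and the diagnosis are already collected, and the sample size need not change. There is one small downside: the adjusted odds ratio is conditional on the covariates and is not the odds ratio from the simple 2×2 table. A standardised risk difference reported beside it gives readers a marginal effect on the scale of the power calculation.
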